**Methods:**

A cluster randomised trial will be implemented in LF-endemic communities in Ghana. The interventions will be yearly or twice-yearly MDA delivered to entire endemic communities. Allocation to study group will be by clusters identified using the prevalence of LF. Clusters will be randomised to one of two groups: receiving either (1) annual treatment with IVM + ALB or (2) annual MDA with IVM + ALB, followed by an additional MDA 6 months later. The primary outcome measure is the prevalence of LF infection, assessed by four cross-sectional surveys. Entomological assessments will also be undertaken to evaluate the transmission intensity of the disease in the study clusters. Costs and cost-effectiveness will be evaluated. Among a random subsample of participants, microfilaria prevalence will be assessed longitudinally. A nested process evaluation, using semi-structured interviews, focus group discussions and a stakeholder analysis, will investigate the community acceptability, feasibility and scale-up of each delivery system.

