### Longitudinal surveys

Individuals who are positive for LF antigen and microfilaria (at baseline) will be followed longitudinally to help quantify the transmission dynamics of LF. They will be asked to provide blood samples 1 month following treatment. Two milliliters of venous blood will be collected in heparinised capillary tubes at night between 9 p.m. and 2 a.m. The collected samples will be transported to the laboratory and analysed. Subsequently, they will be revisited at 3, 6, 9 and 12 months post treatment and asked to provide a sample, which will be examined for the presence of *W. bancrofti* mf [21, 22]. They will also be requested to provide stool samples for the examination of STH infections.

The study team will also conduct household visits to assess the extent of non-compliance to treatment and factors associated with non-compliance [28–33]. The assessment of non-compliance will be based on short, standardised questions, as well as a review of the community drug distribution register.

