The summary statistic for each parasitological endpoint will be estimated, and compared using paired Student’s *t* tests. Changes in rate of infection will be expressed as percentage differences from the pre-treatment rates. The significance in differences in mosquito infection rates will be tested using the chi-square test. The significance of correlation between different indices will also be tested using the chi-square test. The significance of differences in monthly transmission potential before and after treatment will be tested with the non-parametric Mann-Whitney *U* test. Analysis of variance (ANOVA) will also be used in the intent-to-treat analysis for comparing the study groups. SPSS for WINDOWS 16 (SPSS Inc, Chicago, IL, USA) will be used for all statistical computations. The mf intensities will be adjusted for sampling time by multiplying the counts with a time-specific factor [38]. Geometric mean intensities (GMIs) of microfilaraemia and antigenaemia prevalence will be calculated [39].

Below is the statistical analysis strategy.

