### Secondary outcomes

A subsample of 80 individuals from the following clusters: low (1%), medium (2–4%) and high (>5%) LF prevalence; in each of the study groups will be followed longitudinally for 2.5 years in order to better understand the transmission dynamics of LF, and to estimate key parameters for mathematical modelling of transmission dynamics and treatment impact. Both the presence and intensity of *W. bancrofti* mf will be assessed at 3, 6, 9 and 12 months post treatment. Information on covariates that influence *W. bancrofti* mf transmission in humans, such as use of bed nets, will be measured at each of these endpoints.

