#### Analysis strategy

Each of our study outcomes, i.e. prevalence and intensity of *W. bancrofti* mf, will be considered separately during the analysis. Loss to follow-up was taken into consideration during our sample size calculation. Therefore, regardless of the number of incomplete observations, we expect to end up with no less than 58 complete observations per community at the end of the study.

A panel of individual line plots for the study participants would be used in the assessment of within-person variability. Since the assumptions of likelihood are violated by the effect of within-group and within-subject clusters in longitudinal data, in assessing the transmission dynamics of LF infection, the measured covariates will be regressed separately on both the prevalence and the intensity of infections using a quasi-likelihood method, i.e. generalised estimating equations, which uses an association matrix instead of the diagonal matrix employed by the generalised linear models. As part of the model validation, the point-referenced residuals of the provisional models will be assessed for spatial autocorrelation. The results of this assessment would help to determine if unmeasured/unobserved factors in the study areas play relevant roles in the transmission dynamics of LF infections. Using classical geostatistical concepts, our final model would be adjusted for both the effects of the measured and unobserved factors.

For entomological endpoints, infection rates will be determined, using the polymerase chain reaction (PCR) [40] and LAMP [41] methods. The results will be analysed using the poolscreening software by Katholi and colleagues [42, 43].

The findings and data from this study will be used to develop a mechanistic model, which describes the variability in treatment responses in populations. This will be implemented into an already available and well-established transmission dynamic model for LF (LYMFASIM) [44, 45], which will then be used to systematically explore the consequence of twice-yearly treatment on the long-term impact of MDA and elimination prospects. LYMFASIM simulates the spread of *W. bancrofti* in a human community and the impact of control measures, with the advantage of accounting for a variety of parameters specific to the population of interest and output predictions [45, 46].

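### If the longitudinal cohort is chosen for being microfilaria-positive at baseline, its within-arm fall from that baseline partly reflects regression to the mean and should not be read as drug efficacy

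*Protocol article*

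**What the plan says.** The article describes the longitudinal group in three ways.

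- Longitudinal surveys: "Individuals who are positive for LF antigen and microfilaria (at baseline) will be followed longitudinally to help quantify the transmission dynamics of LF". On sampling: "They will be asked to provide blood samples 1 month following treatment". Then: "Subsequently, they will be revisited at 3, 6, 9 and 12 months post treatment and asked to provide a sample". No repeat sample before treatment is described.
- Abstract, Methods: "Among a random subsample of participants, microfilaria prevalence will be assessed longitudinally".
- Secondary outcomes: "A subsample of 80 individuals from the following clusters", followed by low, medium and high prevalence strata in each study group. Being mf-positive is not required.

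On analysis, Data management and analysis gives a general rule: "Changes in rate of infection will be expressed as percentage differences from the pre-treatment rates". The Analysis strategy under Secondary outcomes plans generalised estimating equations (GEE) for prevalence and intensity, and expects at least 58 complete observations per community.

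On use, Study outcomes and measurements and Secondary outcomes both say that the subsample serves "to estimate key parameters for mathematical modelling of transmission dynamics and treatment impact". The Analysis strategy adds that the study's findings and data will be used to "develop a mechanistic model, which describes the variability in treatment responses in populations", which is then built into LYMFASIM. Treatment interventions makes clear that the arms differ only in treatment frequency.

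**The concern.** A single count in 1 ml of night blood varies by chance and from night to night. Carriers who enter because one such count was above zero include some whose count happened to be high that night. At the next visit some of them test negative, and the mean count falls, even if nothing was given. The selecting count is the only pre-treatment value described, so it is also the reference for any change. Everyone is treated, so nothing in the cohort separates the artefact from the drug effect.

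The quantity at stake is the absolute response within an arm. If it were taken at face value as a treatment-impact parameter, each round would look somewhat more effective than it is, and projected elimination would come too early under both schedules.

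**Working it through.** The article states no clearance or efficacy figure for this cohort, so there is nothing to reproduce. The check has four steps. All sensitivities and densities are assumptions, because the article gives none.

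**1. Binary form.** Let s be the chance that one 1 ml sample detects a carrier (specificity 1), and e the true clearance. A cohort selected on one positive sample shows apparent clearance 1 − s(1 − e). The excess over the truth is (1 − s)(1 − e).

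- No drug (e = 0): 30% at s = 0.70, 10% at s = 0.90, 1% at s = 0.99.
- e = 0.765, borrowed only as an illustration from Table 1 in Background (mf-positives 17 to 4 at 3 months, 1 − 4/17): apparent clearance is 0.836, 0.788 and 0.767. The excess runs from 0.3 × 0.235 = 7 points down to 0.01 × 0.235 = 0.2 points.

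**2. Count form.** Simulation of 2,000,000 carriers per scenario. Density is lognormal between people (SD of log 1.5). Night-to-night variation is lognormal and mean-preserving (SD of log 0 to 1). The count in 1 ml is Poisson, and entry requires a baseline count above zero. Excess clearance is the share of the selected cohort negative at follow-up minus the relative fall in prevalence among all carriers. Each range runs from no night-to-night variation to SD 1.

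| Median mf/ml | No drug: retest negative | No drug: fall in geometric mean | True reduction 80%: excess clearance | True reduction 90%: excess clearance |
|---|---|---|---|---|
| 1 | 22–34% | 24–40% | 6–12 points | 3–7 points |
| 3 | 11–21% | 12–26% | 3–8 points | 2–5 points |
| 10 | 4–10% | 4–14% | 1–5 points | 1–3 points |
| 30 | 1–4% | 1–7% | 0–2 points | 0–2 points |

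The geometric mean (count + 1 scale) falls by 79–85% when the true reduction is 80%, and by 88–92% when it is 90%. With a weak drug (true 50%) and medians of 1 to 10, it falls by 51–67%. If night-to-night variation preserves the median instead of the mean, the upper no-drug retest figures drop to 28%, 16%, 7% and 2%. A gamma density model gives 2–25% retest-negative and a 2–32% geometric-mean fall with no drug.

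**3. Between arms.** Selection uses the baseline survey, which precedes randomisation, so s is the same in expectation in both arms. Persistence is s(1 − e) in each arm. The ratio of the two arms is free of s, and the difference is s times the true difference. The artefact can shrink an absolute difference but cannot create one.

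**4. Which cohort?** Expected mf-positives among 1440 participants are 1440 × 0.01 = 14, 1440 × 0.046 = 66, or 1440 × 0.182 = 262. The prevalences come from Sample size calculation (1% to 18.2%) and Background (4.6% mf). Getting 58 complete observations from 80 people per community with mf-positives only would need 58/80 = 72.5% mf prevalence. If 80 means per stratum per arm, 80 × 3 × 2 = 480 are needed, and 480/1440 = 33%. The dataset in the Analysis strategy therefore cannot consist only of mf-positives.

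**The case against.** The strongest reply is that the chain from selection to a wrong elimination forecast is not written down. Two of the three cohort descriptions do not select on mf status, and the 58-per-community expectation rules out an mf-only dataset. The percentage-change sentence is general and does not name this cohort, whose stated analysis is GEE. The model draws on the whole study, and no per-round efficacy input is named. Treatment interventions also presents the regimen as very effective, and with high true efficacy the artefact is small.

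Most of this stands. A reader might infer that the plan feeds an inflated efficacy into the elimination model. The documents do not support that as a stated step. Nor should the no-drug figures (up to 34% retest-negative, up to 40% fall in geometric mean) be read as the inflation to expect, because they describe a drug that does nothing.

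Three things remain. Longitudinal surveys is the only section that gives the field procedure for this group, and it selects on the outcome. The general rule on change makes no exception for it. GEE is no remedy if the selecting baseline is among the repeated outcomes, because the time effect then carries the same artefact.

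**Conclusion.** The point holds conditionally. Under the definition in Longitudinal surveys, a within-arm fall from baseline is partly regression to the mean, and the described design cannot separate the two. It is a risk to the treatment-impact parameters, not a demonstrated error in them. The primary cross-sectional surveys are not selected on mf status and are not affected. The between-arm contrast is largely spared.

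The size rests entirely on assumed densities and night-to-night variation. If the true density reduction is 80% to 90%, excess clearance is about 0 to 12 points, largest at the lowest densities. Such densities are plausible after 13–15 rounds of treatment, but the article does not document them. The bias would be large only if the true response were weak. This is a secondary matter, worth correcting because the correction is cheap.

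**What to change.** 1. Reconcile the cohort definition across the Abstract, Longitudinal surveys and Secondary outcomes, and state which group the 58 complete observations per community refers to.
2. For any cohort selected on mf positivity, state in Data management and analysis and in the Analysis strategy that percentage change from the selecting baseline will not be reported, or passed to the transmission model, as drug efficacy.
3. Use the arm contrast as the main result from that cohort.
4. Estimate within-arm response from a model that conditions on selection: baseline and follow-up counts under one count distribution, with the baseline count zero-truncated. There is no replicate pre-treatment sample, so night-to-night variation cannot be cleanly separated from variable drug response. Report a sensitivity range for it.

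The cost is a somewhat more complex model and a response estimate that is slightly less favourable and less precise, possibly resting on as few as 14 to 66 people. No new samples are needed. Following antigen-positive, mf-negative people as well would help, but it needs extra resources and is optional.

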### Sample size calculation

The sample size was calculated based on the null and alternative hypotheses, together with the type-I and type-II errors defined as follows:

Null hypothesis (H_0_): the additional dose of IVM is not more effective than the standard single dose per annum treatment (i.e. Treatment – Control = 0).

Alternative hypothesis (H_A_): the additional dose of IVM is more effective than the standard dose (i.e. Treatment − Control > 0).

The type-1 error rate (*α*), i.e. rejecting H_0_ when it is true, is set at 0.05, with a two-sided test. To control for type-II error (*β*), the probability of rejecting H_0_ when it is false is set at 0.80, taking into consideration budget allocation.

The hotspot districts have been receiving an annual single dose of IVM for the past 15 years with the prevalence rates ranging between 1% and 18.2%. Therefore, it is assumed that the new intervention would have an effect, expected to be larger than the effect of the standard control approach, with an effect size of 0.4. Based on these assumptions, the sample size was calculated using the Optimal Design software [34]. Thus, for 0.80 power the study requires a cluster size of 58.

With an expected non-response and a loss to follow-up of 37% (determined from previous unpublished studies), the sample size per cluster has been determined to be 80. With 18 clusters to be surveyed, a total of 1440 study participants, from the two study districts, will be expected to take part in this trial.

Study participants will not be paid as part of the survey. However, in order to mitigate the high dropout rates during follow-ups, participants will be compensated for the time lost for working during the days they are participating in survey activities, with an amount of 7 Cedis (equivalent to US$1.61). They will also be contacted at 14 days and 7 days prior to follow-up, in order to ensure their availability. Even though there is always the possibility of emergencies and other social responsibilities that may result in their unavailability, efforts will be made to reach them.

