## Background

Lymphatic filariasis (LF) is a debilitating, mosquito-borne, nematode infection that has been targeted for elimination as a public health problem by 2020. It affects 120 million people in 73 countries where 1.46 billion people are at risk of acquiring the infection through infectious mosquito bites. In 2000, the World Health Organisation, in collaboration with pharmaceutical companies and endemic country governments, launched the Global Programme to Eliminate LF (GPELF). Ivermectin (IVM) in combination with diethylcarbamazine (DEC) or albendazole (ALB) remain the drugs available for the large-scale control of LF [1]. These drugs only temporarily clear microfilariae (mf) without killing all adult worms [2], and it is assumed that a reduction in population mf load will lead to a simultaneous reduction, or even interruption, of transmission [3–5]. It is, therefore estimated, that five to six rounds of mass drug administration (MDA) are required to eliminate the disease. From 2000 to 2014, LF MDA included a cumulative total of 5.62 billion treatments delivered to more than one billion people at least once [6, 7]. Many countries including Ghana have since undertaken between 8 and 15 consecutive annual rounds of MDA in several implementation units without interrupting transmission. In Ghana, where the MDA coverage rates have been more than the required 65%, 29 sentinel sites with persistent residual infections have been identified, with microfilaria prevalence rates of above 1% [8]. Previous studies [9] revealed high prevalence of LF (13% antigen prevalence and 4.6% mf prevalence) in two communities in a district with persistent LF transmission. In these communities, individuals positive for LF were treated and followed at 3-month intervals for 1 year. The results showed a decline in prevalence after treatment, followed by an increase 6 months after treatment (Table 1).

**Table 1 Tab1:** Number of positives and parasite loads at different time points (Unpublished data – [name])

	Dec 2014 (pre treatment)	3 months post treatment	6 months Post treatment	9 months Post treatment	12 months Post treatment
ICT positives	48	17/48 (35.4%)	26/48 (54.2%)	23/33 (69.7%)	15/30 (50%)
mf positives	17/48 (35.4%)	4/48 (8.3%)	4/48 (8.3%)	3/33 (9.1%)	2/30 (6.7%)

*ICT i*mmunochromatographic test, *mf* microfilariae

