## Discussion

The persistent transmission of LF, following years of treatment, represents an important challenge to the LF-elimination programme in Ghana [8], and necessitates the need for additional, alternative strategies in order to achieve the elimination goals. In this study, it is assumed that all community members will actively take part in the MDA programme, in order to achieve high therapeutic coverage. While the selection of study participants is entirely voluntary, it is hoped that many non-compliant individuals will enrol in the study and actively participate in MDA programmes. Poor compliance has been reported in one hotspot district in Ghana [51], and our observations from previous studies in the districts suggest that many infected individuals are generally non-compliant with treatment [9]. An important reason given for non-compliance is the lack of information or inadequate information provided prior to the surveys and treatment [52]. Studies in one hotspot district have also reported low coverage and inaccurate data following MDA [22]. As such, the selection of study subjects will rely on intensive public education activities, informing the study communities on the importance of participating in epidemiological surveys and taking part in MDA. With effective compliance, twice-yearly treatment in high-endemic areas may be considered in reducing the duration of MDA to achieve interruption of transmission [8]. As such, extensive social mobilisation activities will be undertaken as part of the study.

The hotspot districts having received over 15 years of treatment [8] and the LF prevalence in study communities may be low, and thus this represents a challenge to assessing the impact of the intervention. Given sufficient budgetary allowance, the ideal would have been to screen many communities, out of which the study communities would be selected. However, this is not possible within the funding available for the study, and it is assumed that moderate infection prevalence will be obtained in order to evaluate the impact of the intervention.

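### The 0.80 power rests on an effect size of 0.4 with no stated scale; for a prevalence outcome it is not delivered at the lower stated prevalences and needs very large reductions or small clustering at the top

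*Protocol article*

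**What the plan says.** All places are in the Protocol article.

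- Sample size calculation: the type I error "is set at 0.05, with a two-sided test", and power is 0.80. Prevalence under annual treatment is given "with the prevalence rates ranging between 1% and 18.2" per cent. The new schedule's effect is "expected to be larger than the effect of the standard control approach, with an effect size of 0.4". The result, from the Optimal Design software, is that "for 0.80 power the study requires a cluster size of 58". The section gives no scale for 0.4, no pair of prevalences and no ICC.
- Study outcomes and measurements, and Pre-post analysis: the primary outcome is the prevalence of infection, coded 1 or 0 for each person.
- Cluster randomisation: 18 clusters, nine per arm.
- Background: two earlier communities in a persistent-transmission district had "13% antigen prevalence and 4.6% mf prevalence".
- Secondary outcomes: clusters are expected in bands of 1%, 2–4% and above 5%.
- Discussion: the authors accept that "the LF prevalence in study communities may be low" and assume that moderate prevalence will be found.

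**The concern.** An effect size of 0.4 is natural for a mean difference in SD units. For a proportion p, the SD is tied to p, so the largest possible standardised difference shrinks as p falls. The prevalences in the same paragraph go down to 1%, where even total elimination is a small standardised effect. The assumption behind the power figure may therefore be impossible, or very optimistic, for the outcome that it is meant to serve.

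The Discussion expects firm recommendations on twice-yearly treatment. A reader who trusts 0.80 power could take a non-significant result as evidence of no added benefit when the design had little chance of showing a moderate one.

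**Working it through.** **1. Reproducing 58.** Inputs from the protocol: 18 clusters, two-sided 0.05, power 0.80, d = 0.4, n = 58. For a cluster-randomised comparison of standardised means, the noncentrality of the t test on 16 df is

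δ = d / √[(2/9)(ρ + (1 − ρ)/n)].

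The ICC ρ is not stated, so I solved for it. With ρ = 0.0647, the bracket ρ + (1 − ρ)/58 is 0.0808, δ = 0.4/√(0.2222 × 0.0808) = 2.98, and power is 0.80. So 58 is attainable as a standardised difference with an ICC of about 0.065. That is an inference about how the software was used.

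**2. What 0.4 means for a prevalence.**

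- *Absolute difference:* impossible, since the highest stated prevalence is 18.2%.
- *Standardised difference, pooled SD:* with zero infection in the twice-yearly arm, p/√[(p/2)(1 − p/2)] = 0.4 gives p = 0.08/1.04 = 7.7%. Averaging the two variances gives 0.08/1.08 = 7.4%. Below that, elimination falls short of 0.4. At 4.6% the maximum is 0.046/√(0.046 × 0.954/2) = 0.31, and at 1% it is 0.14. At 13%, 0.4 means a fall to 2.4–2.5% (about 81%). At 18.2% it means a fall to 5.3–5.5% (about 70%).
- *Cohen's h:* the threshold is sin²(0.2) = 3.9%. At 4.6%, h = 0.4 means a fall to 0.03% (99%). At 13% it means 2.8% (78%), and at 18.2% it means 5.7% (69%).

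The 1% band and all or nearly all of the 2–4% band are therefore out of reach on either scale. The 4.6% mf figure is out of reach in SD units.

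**3. Power for a binary outcome, nine clusters of 58 per arm.** The noncentrality is (p1 − p2)/√[(v1 + v2)/9]. The per-cluster variance v is p(1 − p)(ρ + (1 − ρ)/58) under an ICC, or p(1 − p)/58 + k²p² under a between-cluster CV of k. Assumed values: ICC 0.01, 0.02, 0.05, 0.065; CV 0.25, 0.5.

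Example: 4.6% to 2.76% (a 40% reduction) at ICC 0.065. The sum of p(1 − p) is 0.0707, the standard error is √(0.0707 × 0.0811/9) = 0.0252, the noncentrality is 0.0184/0.0252 = 0.73, and power is about 0.11.

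| Control prevalence | Power, 40% relative reduction | Power, odds ratio 0.4 | Smallest whole-percent reduction with 80% power |
|---|---|---|---|
| 1% | 0.06–0.10 | 0.08–0.19 | none (elimination: 0.17–0.56) |
| 4.6% | 0.11–0.28 | 0.19–0.59 | 73–92%; none at ICC 0.05 or 0.065 |
| 13% | 0.22–0.58 | 0.43–0.90 | 51–81% |
| 18.2% | 0.31–0.71 | 0.55–0.95 | 45–70% |

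A 40% relative reduction never reaches 0.80. An odds ratio of 0.4 reaches it only at 13% (ICC 0.01: 0.87; CV 0.25: 0.90) and at 18.2% (ICC 0.01: 0.95; ICC 0.02: 0.87; CV 0.25: 0.94).

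**4. Elimination from 4.6%.** Power is 0.58 at ICC 0.065, 0.90 at ICC 0.02, and 0.95–0.99 at CV 0.5–0.25.

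**The case against.** A reader might infer that 0.4 can never be reached at the stated prevalences, or that the trial is underpowered whatever happens. The documents do not support either reading. At 13% and 18.2%, 0.4 is reachable, though only with reductions of about 80% and 70%. Halving 18.2% at ICC 0.01 has power 0.90. The 0.58 for elimination from 4.6% holds only at the back-solved ICC. At 4.6%, an ICC of 0.065 corresponds to a CV of √(0.065 × 0.954/0.046) = 1.16, well outside the CV range used here.

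Other points for the plan:

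- No arithmetic slip is shown: 58 follows from d = 0.4 at a plausible ICC. The article condenses a full protocol that may give the ICC and the prevalence pair, so their absence here is not the point.
- The calculation above ignores stratified randomisation, covariate adjustment and the analysis against baseline. These may raise power by an amount that cannot be quantified from the article.
- Cluster randomisation describes 45 households with five members each, or 225 per cluster, which does not match the 80 in the sample size section. At 225, an odds ratio of 0.4 at 4.6% has power 0.96 at CV 0.25, 0.72 at CV 0.5 or ICC 0.01, and 0.21 at ICC 0.065. I used 58 because the power claim and the Analysis strategy section both rest on it.
- The Discussion already warns of low prevalence.

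These points limit the conclusion to part of the range but do not remove it. The Discussion's warning does not withdraw the 0.80 figure. No detail held elsewhere can make 0.4 SD attainable at 4.6%.

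**Conclusion.** Wrong as written. The 0.80 power is stated without qualification, but the assumption behind it does not fit a 1/0 outcome over much of the prevalence range in the same paragraph. On a standardised scale, 0.4 exceeds complete elimination below about 7.7% (about 3.9% on Cohen's h). At the top of the range it implies about a 70% or larger reduction beyond an annually treated control. If a 40% relative reduction was meant, power is at most about 0.71.

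The supportable conclusion is that 0.80 is not delivered at the lower stated prevalences and is conditional at the higher ones. It is not that the trial lacks power in every case. The figures assume 58 analysed per cluster, nine clusters per arm, an unadjusted comparison, and ICC 0.01–0.065 or CV 0.25–0.5. The clustering values are assumptions, and the ICC of 0.065 is inferred.

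**What to change.** Replace the effect-size and 0.80-power sentences with:

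1. the assumed control-arm prevalence of the named marker (antigen or mf), as a range;
2. an assumed ICC or between-cluster CV, with its source;
3. nine clusters per arm and the number expected to be analysed in each;
4. the minimum detectable relative reduction at 80% power over that range. At 58 per cluster, under the assumptions above, this is about 45–70% at 18.2%, 51–81% at 13%, and 73–92% at 4.6% (unattainable there at ICC 0.05 or 0.065). No reduction is detectable with 80% power at 1%.

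Add a sentence that a null result at low prevalence will not be taken to show that the two schedules are equivalent.

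The cost is a recalculation and less favourable published figures. No extra participants or procedures are needed.

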### Study outcomes and measurements

The primary outcome, the prevalence of LF infection, will be measured through cross-sectional parasitological surveys conducted at baseline and at 12, 24 and 30 months’ follow-ups. Figure 1 presents a flowchart of the study design. The timing of the final follow-up survey will take into account differences in time since treatment of the annual and biannual treatment groups at 24 months. The time point assessments at 12, 24 and 30 months will allow us to evaluate changes in the primary study outcome in the intervention and control groups over time. For secondary outcomes, a subsample of individuals from the clusters in each of the study groups will be followed longitudinally for 2.5 years in order to better understand the transmission dynamics of LF and to estimate key parameters for mathematical modelling of transmission dynamics and treatment impact. The impact of treatment on other STHs (roundworm (*Ascaris lumbricoides*), whipworm (*Trichuris trichiura)*, and the hookworms (*Ancylostoma duodenale* and *Necator americanus*) and any other species identified) will also be assessed. A nested process evaluation, using semi-structured interviews, focus group discussions (FGDs) and a stakeholder analysis, will investigate the community acceptability, feasibility and participation in the twice-yearly drug administration. The local and regional health system structures and processes will be evaluated to determine the feasibility to scale-up the interventions.

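### The promise of at least 58 complete observations per community at the end of the study fails at the plan's own 37% loss, which leaves about 50 of 80, and the 37% has no stated time point

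*Protocol article*

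**What the plan says.** Under Sample size calculation, the type I error "is set at 0.05, with a two-sided test", and "the probability of rejecting H_0_ when it is false is set at 0.80". The calculation is made "with an effect size of 0.4", and the result is that "for 0.80 power the study requires a cluster size of 58". No intracluster correlation is given. The allowance follows: "With an expected non-response and a loss to follow-up of 37% (determined from previous unpublished studies"), after which "the sample size per cluster has been determined to be 80". With 18 clusters this gives 1440 participants, which is also the target in Table 2. No time point is attached to the 37%.

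Under Study outcomes and measurements, the primary outcome comes from cross-sectional surveys "conducted at baseline and at 12, 24 and 30 months". The Pre-post analysis section nevertheless models each participant's change from baseline to follow-up and plans a mixed model for repeated measurements per individual.

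The Analysis strategy under Secondary outcomes says that loss was allowed for in the sample size and that, however many observations are incomplete, "we expect to end up with no less than 58 complete observations per community at the end of the study".

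Table 1 (Background, unpublished data) shows 48 LF-positive people, of whom 48 were examined at 3 and 6 months, 33 at 9 months and 30 at 12 months.

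**The concern.** The statement about 58 is the document's answer to the question of incomplete data, and it is worded as a floor that holds whatever the loss. A floor of 58 from 80 requires loss below 28%, yet the plan itself expects 37%. A reader who relies on the floor would take the 0.80 power as protected to the end of the trial and would see no need to plan for a smaller analysed set.

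The lack of a time point adds to this. If the same people are followed to month 30, the loss that matters is the loss by month 30, and nothing in the document says that the 37% reaches that far. Heavy loss in an open-label trial also leaves room for selective follow-up, which a claimed floor of 58 would hide.

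**Working it through.** **Inputs.** Required cluster size 58, allowance 37%, stated cluster size 80, 18 clusters, effect size 0.4 and two-sided alpha 0.05 (all Sample size calculation). Numbers examined in Table 1: 48, 48, 33 and 30 at 3, 6, 9 and 12 months. The intracluster correlation is not given.

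**1. Reproducing the plan's 80.** 58 x 1.37 = 79.46, rounded up to 80; 80 x 18 = 1440. The stated figures are reproduced when the allowance is added to 58. Dividing by the retained fraction gives 58/0.63 = 92.06, rounded up to 93, which is not the stated figure.

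**2. What 80 delivers.** Largest loss that still leaves 58: 1 - 58/80 = 27.5%. At 37%: 80 x 0.63 = 50.4 per village, and 1440 x 0.63 = 907 in total. The shortfall is about 8 per village, whatever period the 37% covers.

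**3. The only follow-up data shown.** Table 1 at 9 months: (48 - 33)/48 = 31.25% not seen. At 12 months: (48 - 30)/48 = 37.5% (exact 95% interval 24% to 53%). In that group the 27.5% tolerance was passed by month 9.

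**4. Power.** For a two-arm cluster comparison with J = 18 clusters of n and intracluster correlation rho, the F test on 1 and 16 degrees of freedom has noncentrality J x 0.4² / (4 x [rho + (1 - rho)/n]). Setting power to 0.80 at n = 58 gives rho = 0.065. This is a back-solved assumption, not a figure from the document. With it, and with loss levels above 37% that are assumed for illustration:

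| Loss | Remaining of 80 | Power |
|---|---|---|
| 27.5% | 58 | 0.80 |
| 37% (the plan) | 50.4 | 0.79 |
| 45% | 44 | 0.78 |
| 50% | 40 | 0.77 |
| 60% | 32 | 0.74 |
| 69% | 25 | 0.70 |

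The last row carries the 12-month retention of Table 1 forward at a constant rate: (30/48)^2.5 = 0.309, and 80 x 0.309 = 24.7. It is a pessimistic bound only.

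The move from 58 to 50 costs about 0.01 at nearby correlations too: 0.871 to 0.858 at rho = 0.05, and 0.730 to 0.719 at rho = 0.08. Power changes slowly because the number of clusters dominates.

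**The case against.** **A tempting stronger reading.** A reader might infer that the 37% is the 12-month loss of Table 1 (18 of 48) applied by mistake to a 30-month trial. The figures are close and both sources are called unpublished. But the sample size section cites studies in the plural, combines non-response with loss, gives no time point and does not refer to Table 1. Table 1 covers 48 treated LF-positive people in two communities and has no non-response component. The match suggests a one-year origin and does not show it. Nor is 69% loss at month 30 supported: the Table 1 counts do not fall at a constant rate, a missed visit need not be permanent, and the protocol plans compensation and reminders to limit dropout.

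**The surveys are called cross-sectional.** With a fresh sample each time, loss would not build up. This is a fair point against any accumulating figure. It is not a full answer, because the Pre-post analysis needs the same individuals, the sample size section speaks of dropout during follow-ups, and no redraw of households is described. It also leaves the 80 x 0.63 result untouched.

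**Part of the 37% may be non-response.** If 80 were the number enrolled after refusals were replaced, the loss component alone might stay under 27.5% and 58 could be met. The document does not split the figure and derives 80 by applying all of it. This is a reason to ask for the split, not a basis for a guarantee.

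**The starting number may not be 80.** The Cluster randomisation section selects 45 households per cluster and recruits five eligible members. Read as five per household, that is 225 per cluster, and 58 would be safe. But this conflicts with 80 per cluster and with the target of 1440, both stated outright.

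**The sentence sits under Secondary outcomes.** It may concern the longitudinal subsample. That subsample is followed for 2.5 years, and the sentence relies on the same sample size calculation, so the 27.5% limit applies on either reading.

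**Conclusion.** The point holds for the guarantee. From 80 per village, 58 complete observations need loss of at most 27.5%; the plan's own 37% leaves about 50 per village, about 907 of 1440. This rests on taking 80 as the starting number and the whole 37% as coming off it, which is how the plan uses both. The effect on power is small at that loss: about 0.79 against 0.80, given the back-solved correlation of 0.065.

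The time horizon stands only as a query. If the 37% is a one-year figure and the same people are followed to month 30, loss could be larger and power lower, for example 0.74 at 60% loss. The document does not establish either condition.

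**What to change.** - In the Analysis strategy under Secondary outcomes, delete the statement that no fewer than 58 complete observations per community will remain. Replace it with about 50 per village (about 907 of 1440) at 37% loss, and power just under 0.80, with the intracluster correlation that was used.
- In Sample size calculation, give the source and time point of the 37% and split it into non-response and loss to follow-up.
- If the same individuals are followed to month 30, give the expected number and power at months 24 and 30 over a stated range of loss, such as 45% (44 remain) to 60% (32 remain), with 69% (25 remain) shown only as a pessimistic bound.
- If each survey instead draws a fresh sample to 80, say so and reconcile this with the paired, repeated-measures analysis in the Pre-post analysis section.

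This costs wording and a short recalculation, and the stated end-of-study size becomes slightly less favourable. Keeping 58 at 37% loss would instead take 93 per cluster, 18 x 93 = 1674 in total, which is 234 more people in a trial that is already recruiting.
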